## Abstract

**Background:**

Autistic people commonly have physical and mental health conditions. They also frequently experience barriers to accessing healthcare, contributing to problems identifying and treating health conditions. These factors may lead to increased and earlier morbidity and lower average life expectancy for autistic people. Health checks specifically designed for autistic people, incorporating adjustments to healthcare, may help to overcome these barriers and reduce health inequalities. This trial aims to investigate the clinical and cost-effectiveness of a primary care health check for autistic adults and explore factors related to implementation such as acceptability and feasibility of delivery. The trial is co-designed and delivered by health professionals, autistic people, carers and supporters, and researchers.

**Methods:**

This is a clinical and cost-effectiveness, cluster randomised controlled trial of a primary care health check for autistic adults. Primary care practices will be randomised into one of two groups (intervention or control). Two hundred autistic adults (aged 18 years and over) who provide baseline data will be recruited via participating practices. Data will be collected through quantitative and qualitative methods. The primary outcome will be the incidence of new health needs/conditions detected and met at 9 months (data gathered from participant’s GP records). Secondary outcomes will include the following: cost-effectiveness, measured as incremental cost per quality-adjusted life year gained over 9 months; the extent of health monitoring and health promotion needs met at 9 months; the incidence of social care needs identified at 9 months; changes in participant or carer general health; changes in quality of life; primary and secondary health and social care resource usage and costs. A qualitative study will explore views about the acceptability of the health check, its utility and future use.

**Discussion:**

This study will examine the effectiveness and cost-effectiveness of a primary care health check for autistic adults in identifying new health conditions and needs. If the intervention is effective, it would provide strong evidence for implementation into routine healthcare, therefore enabling earlier health condition diagnosis and opportunities for treatment, reducing the health inequalities experienced by autistic people.

**Trial registration:**

ISRCTN, retrospectively registered on 20 July 2023. https://www.isrctn.com/ISRCTN30156776 (ISRCTN registration number: 30156776).

**Supplementary Information:**

The online version contains supplementary material available at 10.1186/s13063-024-08641-5.

## Background

Autistic people^1^ experience more physical and mental health conditions than non-autistic people and premature mortality [1–5]. Several studies have highlighted a range of barriers faced by autistic adults in accessing healthcare services, which likely contribute to difficulties in identifying and treating autistic adults’ health conditions [6]. These include problems with patient-provider communication [7], a lack of autism training among healthcare providers [8], sensory overload due to healthcare environments [9], cognitively inaccessible systems and services, and a lack of adequate support [10, 11]. Health checks identify some important conditions that affect health and wellbeing and are available to some groups of people in several countries. Regular health checks designed for autistic people, incorporating adjustments to healthcare practices, may help to overcome these barriers and reduce health inequalities for autistic people.

Annual health checks for people with intellectual disabilities^2^ were developed and evaluated in several Randomised Controlled Trials (RCTs) [12, 13], leading to arrangements being put in place for people with intellectual disabilities to receive an annual health check within primary healthcare services. Recent studies found that health checks for people with intellectual disabilities consistently identified unmet health needs, resulted in targeted actions to address those needs, and reduced mortality [12–16]. However, these may not be available to or appropriate for autistic people who do not have an intellectual disability. The development and implementation of a health check specifically for autistic adults might bring similar benefits.

Approaches that are similar to a health check for autistic people have been developed in the US and Australia. AASPIRE (Academic-Autism Spectrum Partnership in Research and Education) developed the AASPIRE Healthcare toolkit [10] to support autistic people in accessing primary care and to support primary care health professionals (hereafter health professional) in meeting the health needs of autistic people. This includes the Autism Healthcare Accommodations Tool (AHAT), which creates a customised ‘accommodations report’ for individuals to share with their healthcare providers highlighting things that would make healthcare easier for the individual. Evaluation of the AHAT in the US found that it significantly reduced barriers to healthcare and increased ratings of patient-provider communication and patient healthcare self-efficacy [10]. In Australia, use of the AASPIRE Healthcare toolkit [10] was explored with six autistic adults who reported the toolkit facilitated their interactions with health professionals and that an adapted version specific for the Australian context may be beneficial [17]. Also in Australia, the Comprehensive Health Assessment Program (CHAP) was developed to provide a health check for people with intellectual disabilities [13]. This has subsequently been adapted for autistic adults and adolescents and its effectiveness is being evaluated.

Autistic people, supporters, and professionals have agreed that the creation and evaluation of a health check for autistic people is a priority to address healthcare access and the possible impact of healthcare barriers on wellbeing and life expectancy as research priorities [18]. Policy makers have also identified the development and evaluation of health checks for autistic people as a priority [19, 20]. To address this research priority, we designed a research programme with three stages: first, we identified the facilitators and barriers to healthcare access for autistic adults through group discussions and interviews with autistic people, supporters, and health professionals [6, 21]. Second, we created a health check for autistic people in partnership with autistic people, carers and supporters, and health professionals [21, 22]. This comprised primary care training, a health checklist, and a questionnaire (online and paper) to be completed by autistic people prior to the appointment and used to gather health-related information and the adjustments needed to make the appointment most acceptable. The final stage of the programme is the cluster randomised control trial (RCT), described below.

### Objectives

The aim of this cluster RCT is to evaluate the clinical and cost-effectiveness of a health check for autistic adults compared to usual care at 9 months follow-up. We will assess the clinical effectiveness of this intervention by measuring the incidence of new health needs and conditions detected and met at 9 months. There are a number of secondary outcomes including (i) the extent of health monitoring and health promotion needs being met at 9 months, (ii) changes in participant or carer-related general health and quality of life, (iii) the incidence of social needs identified at 9 months, (iv) changes in primary and secondary health and social care resource usage and costs, and (v) incremental cost per quality-adjusted life year (QALY). A qualitative study will also explore views about the acceptability of the health check, its utility and future use.

## Methods and design

### Study design

This study is a two-group cluster RCT non-blinded to participants but blind to the outcome assessors. Primary healthcare services (National Health Service general practices, referred to as ‘practices’ from hereon) will be randomised to either deliver the health check for autistic adults (intervention arm) or provide usual care (control arm), in keeping with previous research methods from published research, and following discussion with autistic people during the research design stage. We will offer adults aged 18 years or above with a clinical diagnosis of autism spectrum disorder at participating practices the opportunity to take part. We will administer assessments on entry to the trial (baseline) and at 3 months, 6 months, and 9 months after the health check, for the intervention arm, or after baseline measures are completed, for the usual care group. We will also gather qualitative data on the acceptability and feasibility of the health check to inform its future use. See Additional File 1 for Standard Protocol Items: Recommendations for Interventional Trials (SPIRIT) checklist for study.

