The practice will invite autistic participants to attend a health check appointment after their Health Check PAQ is received. Autistic participants will receive a leaflet containing details about the health check appointment. An appropriate health professional will complete the Health Check appointment, taking account of the information in the Health Check PAQ Summary Report. The Health Check appointment covers health promotion, health screening, vaccinations, physical health, mental health, daily functioning, relationships and sexual health, a brief medication review, and a physical examination. The health check appointment takes around 45 min to complete. Practices will offer flexibility around how the health check appointment is conducted (i.e. face-to-face, via video, via telephone or home visit) in line with the autistic participant’s preference and needs. The health professional will always undertake the physical examination in a face-to-face appointment. The health professional will communicate a Health Action Plan to the autistic participant at the appointment (with a written copy offered) based on the discussions, including highlighting the needs identified. They will also arrange any tests, interventions, or onward referrals as part of NHS care based on the Health Action Plan.

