#### Outcome measures

The primary outcome for the trial will be the incidence of new health needs or conditions detected and met at 9 months. The primary analysis will report the mean number of identified needs that are met for each group. A number of secondary outcomes will also be evaluated including the following: the extent of health monitoring and health promotion needs met at 9 months, the incidence of social needs identified at 9 months, change in participant or carer general health, changes in quality of life, and changes in primary and secondary health and social care resource usage and costs. The primary economic outcome will be the incremental cost per QALY gained at 9 months.

Effectiveness measures:Bespoke Health Records Data Collection Form: we will collect health and social data routinely recorded by practices alongside information about previous health checks and health screening. This was informed by data collection from Cooper et al. [12] and includes the following: short and medium term health outcomes including number and type of new health needs/new conditions/new manifestation of an existing or previously diagnosed condition identified, any referrals to secondary care and/or general hospitals and results, screening or treatments undertaken (including management of Quality & Outcomes Framework qualifying long term conditions and review of medications or other treatment plans), and whether these health needs/conditions were resolvedPrimary Care Outcomes Questionnaire (P-COQ [29]) is a standardised 24-item questionnaire to measure outcomes in primary care. Analysis has identified 4 domains (health and wellbeing, health knowledge and self-care, confidence in health provision, and confidence in health plan) with high levels of internal consistency across each domain (Cronbach’s *α* = 0.77–0.95) and correlate with comparator Patient-Reported Outcome Measures (PROMs)Bespoke Lifestyle Outcomes Questionnaire gathers information about lifestyle choices and health related behaviours

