Acceptability and feasibility measures:Bespoke Health Check Evaluation Questionnaire gathers information about the experience of completing/receiving the Health Check PAQ and attending/delivering the health check appointment. This questionnaire will only be completed by those in the health check arm immediately after the health check. There are parallel versions for autistic adults, carers and supporters, and health professionalsAppointment acceptance and attendance rates: we will collect data on the acceptance of health check appointments in the health check arm. We will use a brief questionnaire to ask participants who did not attend an offered health check appointment why they did not attend

Digital tool measures:

Information about the digital version of the Health Check PAQ, e.g. time taken to complete and whether completed in one visit: We will gather data using a Health Check Evaluation Questionnaire and semi-structured interviews post-health check

Health economic measures:EQ-5D-5L [30] [31] is a standardised measure of health-related quality of life allowing for the calculation of QALYs, used by NICE routinely to measure intervention effectiveness [32]. There is evidence that the measure demonstrates convergent validity with all items of the World Health Organisation Five Wellbeing Index (WHO-5 [33])Short-Form Health Survey version 2 (SF-36v2) [34]) is a standardised measure of health-related quality of life. The SF-36v2 assesses eight health concepts: limitations in physical activities because of health problems, limitations in social activities because of physical or emotional problems, limitations in usual role activities because of physical health problems, bodily pain, general mental health (psychological distress and wellbeing), limitations in usual role activities because of emotional problems, vitality (energy and fatigue), and general health perceptions. The SF-36v2 has high precision and has been extensively validated as a tool to measure health-related quality of lifeBespoke Health Resource Usage Questionnaire: to capture data on primary and secondary healthcare resource usage, use of social services and prescribed medicationBespoke Time and travel costs questionnaire: to capture time and travel costs related to contacts with healthcare providers

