### Data analysis plan

#### Statistical analysis for quantitative analysis

We will carry out all statistical analyses in accordance with the intention-to-treat principle where all participants’ outcomes are analysed as randomised. We will report all participant flow in accordance with CONSORT statement for non-pharmacological interventions. A full statistical analysis plan will be written and signed-off before trial statisticians receive any unblinded data. The following represents a summary of the planned analyses.

The underlying structure of the data displays a two-level hierarchical structure, in which one level (participants) is nested within another (practices). Members of the same practice share contextual factors and GP conduct, meaning 2 people of the same practice are more likely to have similar data relative to two people from different practices. This clustering effect can be measured using the intra class correlation coefficient (ICC). To compare the groups for the primary outcome, taking into account the clustering effect, we will use a mixed-effects Poisson regression model that has fixed effects for cluster size, treatment allocation, age, and sex. If this model does not converge, we will reduce the number of fixed effects in the model and then (if it still does not converge) change the random cluster effect to a fixed effect.

We will conduct subgroup analyses for the primary outcome by including the subgroup variable and an interaction parameter between subgroup variable and intervention. The subgroups we will investigate are number of conditions at baseline (above median vs median or below) and presence vs absence of mental health condition at baseline.

For secondary outcomes, we will use appropriate mixed-effects regression models, depending on the outcome type. If the outcome is a questionnaire that is also assessed at baseline, the model will adjust for that baseline measure.

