Participants who withdraw consent for the collection of routinely available data prior to month 9 will not be included in the primary outcome analysis. We do not anticipate there being missing data for the primary outcome as it is based on routinely collected data. Secondary analyses will be complete-case analyses. For outcomes that are significant, if there is substantial differential dropout between treatment groups, we will apply multiple imputation with at least 20 imputed datasets and undertake sensitivity analyses to explore the robustness of results to the missing not at random assumption. We will record and tabulate the number of serious adverse events per group.

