#### Economic evaluation

The economic evaluation will involve a within-trial economic evaluation to estimate the incremental cost per QALY gained at 9 months. The analysis will take the perspective of the UK National Health Service (NHS) and Personal Social Services. We will consider a wider societal perspective by analysing the costs borne by the participants and their carers. For the within trial economic evaluation, QALYs will be estimated from responses to the EQ-5D-5L administered at baseline and 3, 6, and 9 months follow-up. As per the National Institute for Health and Care Excellence (NICE)’s current guidelines [35], the EQ-5D-5L results will be converted (‘cross-walked’) into EQ-5D-3L scores. These values will be used to estimate QALYs for each participant using the area under the curve approach [36]. In a sensitivity analysis, QALYs will also be estimated from responses to the SF-36v2 administered at the same time points. The responses to the SF-36v2 will be converted into SF-6D tariffs [37] and QALYs estimated using the same methodology as described above.

Intervention cost data: The cost of delivering the health check in primary care will be calculated using the information captured by the Health Check Evaluation Questionnaire. This includes data relating to the training required for delivering the health check and the time and resources for delivering the health check appointment and creating the health action plan.

Resource use data: The costs of all health services will be estimated using routine data sources, e.g. Unit Costs of Health & Social Care for primary and social care [38], NHS National Schedule of Reference Costs, and the British National Formulary for medications [39]. For each participant, we will combine measures of the use of resources with unit costs to provide a cost for that participant and mean cost at 9 months for each randomised group.

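### Follow-up is timed from the health check in one arm and from baseline in the other, so the 9-month count, QALYs and costs lack a common window and non-attenders have no stated month 9

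*Protocol article*

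**What the plan says.** Under Study design, the protocol article places the first assessment at trial entry in both arms: "We will administer assessments on entry to the trial (baseline) and at 3 months, 6 months, and 9 months". It then gives the later time points a different start in each arm: "9 months after the health check, for the intervention arm, or after baseline measures are completed, for the usual care group".

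Under Health check for autistic adults intervention, several steps separate baseline from the check. The practice sends the pre-appointment questionnaire, the participant returns it, and only then comes the invitation: "The practice will invite autistic participants to attend a health check appointment after their Health Check PAQ is received". No usual or maximum interval is given.

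The outcomes are nevertheless described as 9-month quantities common to both arms. Under Outcome measures: "The primary outcome for the trial will be the incidence of new health needs or conditions detected and met at 9 months", to be reported as a mean number per group. Under Economic evaluation: "QALYs will be estimated from responses to the EQ-5D-5L administered at baseline and 3, 6, and 9 months follow-up", with an area-under-the-curve calculation and a mean cost at 9 months per group.

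Non-attendance is expected: "We will use a brief questionnaire to ask participants who did not attend an offered health check appointment why they did not attend". The analysis is to be "in accordance with the intention-to-treat principle where all participants’ outcomes are analysed as randomised". The one exclusion stated for the primary analysis is itself tied to month 9: "Participants who withdraw consent for the collection of routinely available data prior to month 9 will not be included in the primary outcome analysis".

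**The concern.** The primary outcome is a count of needs detected and met, and a count grows with the time observed. The two arms can be compared only if each participant's window is fixed in the same way, by something that does not depend on allocation or on what happens afterwards. Here the anchor depends on allocation. In the intervention arm it is an event after randomisation that some participants never reach, and it is also the occasion on which many needs are likely to be recorded.

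Three things are at stake: whether the primary count ratio is a fair comparison, whether everyone randomised has a defined outcome, and whether the incremental cost per QALY compares equal spans of time.

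**Working it through.** **Inputs from the article.** The nominal follow-up is 9 months. There are about 100 participants per arm: the stated inflation is 200 × 1.10 = 220, and 10% attrition leaves 220 × 0.90 = 198. The listed fixed effects of the Poisson model are cluster size, allocation, age and sex.

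**Inputs assumed because the article does not give them.** Lag L of 1, 2 or 4 months; control mean μ of 1.5 to 3 needs per 9 months; design effect DE of 1 to 2; two-sided 5% test; utility 0.6 to 0.8.

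**Reading A: needs counted from baseline.** The windows are 9+L and 9 months. With a constant event rate and no effect of the check:

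- Ratio R = (9+L)/9: 10/9 = 1.11, 11/9 = 1.22, 13/9 = 1.44.
- SE of log R = √[DE × (1/(100μ) + 1/(100μR))].
- False-positive rate = Φ(log R/SE − 1.96) + Φ(−log R/SE − 1.96).

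Example for L = 2, μ = 1.5, DE = 2: SE = √[2 × (1/150 + 1/183.3)] = 0.156; log R = 0.201; log R/SE = 1.29; rate = 25%.

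| L (months) | R | μ 1.5, DE 2 | μ 1.5, DE 1 (same as μ 3, DE 2) | μ 3, DE 1 |
|---|---|---|---|---|
| 1 | 1.11 | 10% | 15% | 26% |
| 2 | 1.22 | 25% | 45% | 73% |
| 4 | 1.44 | 69% | 93% | 99.8% |

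At L = 0 the ratio is 1.00 and the rate is 5%.

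**Reading B: needs counted from each arm's own anchor.** Both windows last 9 months, so the ratio from window length is 9/9 = 1.00 and the table does not apply. The windows still differ in kind. The intervention window opens at a detection event after randomisation and drops any need recorded between baseline and the check. The control window opens at an ordinary date and drops nothing after baseline. The documents give nothing from which to size this.

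**Non-attenders, either reading.** Month 9 in the intervention arm is defined as 9 months after the check. A participant with no check has no month 3, 6 or 9 on that definition. The article expects such participants and keeps them in the analysis. The rule on withdrawal before month 9 is also undefined for them.

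**QALYs.** From the baseline EQ-5D-5L to the last one is 9+L months in the intervention arm and 9 in control.

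- Actual dates without a cut: the extra QALY at constant utility u is u × L/12. At L = 2 that is 0.6 × 2/12 = 0.10 to 0.8 × 2/12 = 0.13, against a 9-month total of 0.45 to 0.60.
- Nominal dates: no extra time is added, but the intervention baseline value is placed L months too late.

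**The case against.** The best defence is that equal 9-month windows, each from its own anchor, fit the article's repeated references to outcomes at 9 months. On that reading the ratios and false-positive rates above vanish. This stands as a limit on the size of the problem. It leaves the unlike anchors and the undated non-attenders.

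Four stronger conclusions are tempting, and the documents do not support them:

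- **The count is biased towards the health check.** This follows only if needs are counted from baseline, and the article does not say where record extraction starts.
- **Non-attenders are dropped.** No text excludes them, and the intention-to-treat statement retains them. The gap is that the stated schedule does not date them. The time-point figure is not available here and might do so.
- **The model wrongly omits a person-time term.** The analysis section calls itself a summary and defers to a full analysis plan, where an offset may sit. An offset would adjust for window length but would not give the arms a common origin.
- **The trial dates show long waits.** The last participant was recruited on 21 March 2024, and qualitative recruitment of staff and carers ran to 31 July 2024, 132 days later. Staff are approached after health checks with no time limit, so this gap does not measure the interval from baseline to check.

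It is also fair to say that an origin at baseline has a price. The outcome requires needs to be met as well as detected, and a long wait leaves less time for that.

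**Conclusion.** The point holds in conditional form. It is certain that the two arms have different time zeros, because Study design says so, and that this schedule gives participants who never attend no month 9. Neither reading of the count gives a comparable window.

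The size is not known. If needs are counted from baseline, the null ratio is 1.11 to 1.44 for lags of 1 to 4 months, and even the mildest scenario shown (1 month, mean 1.5, design effect 2) doubles the nominal 5% error. If they are counted from the check, the distortion is real in kind but cannot be sized. The added 0.10–0.13 QALY applies at a 2-month lag with actual dates left uncut; nominal dates give a mis-timed curve instead. All these figures rest on assumed lag, event rate, clustering and utility.

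The primary comparison, the intention-to-treat set and the cost-effectiveness result all depend on this choice, so it should be settled before unblinded data are seen.

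**What to change.** For the primary analysis, use one origin in both arms: the date on which baseline measures are completed.

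- **Primary count.** Include needs dated in the GP record from baseline to baseline + 9 months, for every participant whether or not the check took place. Where follow-up is partial and consent allows use of the data already held, include the observed time through a log person-time offset.
- **QALYs and costs.** Build both on actual dates and cut them at 9 months from baseline in both arms. Interpolate utility between the assessments on either side, and apportion questionnaire-based costs over their recall period.
- **Non-attenders.** State that month 9 runs from baseline. Where their questionnaires can still be scheduled, time them from baseline; otherwise analyse by the dates on which they were completed.
- **Supplementary analysis.** Keep the window of 9 months after the check for attenders, labelled as such.

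Reconcile Study design with Outcome measures, the statistical analysis section and Economic evaluation accordingly.

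**Cost.** For the count, the change is wording in the analysis plan and a date filter, provided that record entries are dated. The sample size does not change. Recruitment closed on 21 March 2024, so changes to questionnaire timing may be limited. The statistical price is less time after the check for needs to be met: 9 − L months, that is 8, 7 or 5 at lags of 1, 2 or 4 months. The estimated effect is diluted to some degree, more so as the wait lengthens, and the supplementary analysis shows what happens with the full period after the check.
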